## Abstract

**Background:**

We describe the theoretical rationale and protocol for Self-Help And Recovery guide for Eating Disorders (SHARED), a trial investigating whether a guided self-care intervention (*Recovery* MANTRA) is a useful addition to treatment as usual for individuals with anorexia nervosa. *Recovery* MANTRA*,* a 6-week self-care intervention supplemented by peer mentorship, is a module extension of the Maudsley Model of Treatment for Adults with Anorexia Nervosa and targets the maintenance factors identified by the cognitive-interpersonal model of the illness.

**Methods:**

Patients accessing outpatient services for anorexia nervosa are randomized to either treatment as usual or treatment as usual plus *Recovery* MANTRA. Outcome variables include change in body weight at the end of the intervention (primary) and changes in body weight and eating disorder symptoms at immediate and extended follow-up (6-months; secondary). Change is also assessed for the domains identified by the theoretical model, including motivation, hope, confidence to change, positive mood, cognitive flexibility, therapeutic alliance and social adjustment. Feedback from peer mentors is gathered to understand the impact on their own well-being of providing guidance.

**Discussion:**

Results from this exploratory investigation will determine whether a larger clinical trial is justifiable and feasible for this affordable intervention, which has potential for high reach and scalability.

**Trial registration:**

ClinicalTrials.gov NCT02336841.

### Theoretical underpinnings for *Recovery* MANTRA

According to the cognitive-interpersonal model of eating disorders [9,10], abnormal eating behaviours in anorexia nervosa are maintained through four factors: (a) positive beliefs about the utility of the illness; (b) a rigid, detail-focused thinking style; (c) avoidance of the experience and expression of emotion; and (d) problematic interpersonal relationships [10]. These elements are thought to develop into habits through a process of neuroadaptation to the illness [11,12]. The *Recovery* MANTRA manual offers a shorter and more focused version of the workbook originally developed for the Maudsley Model of Treatment of Adult Anorexia Nervosa (MANTRA) [13,14]. The *Recovery* MANTRA programme consists of four different intervention modules that target difficulties associated with cognitive processing, emotional functioning, interpersonal style, and poor nutrition. The overall content is aimed at reversing eating disorder habits by making non-eating disorder behaviour more automatic through processes that increase awareness, planning and behavioural experiments [15-17] delivered through a motivational interviewing framework. Moreover, intervention materials are available for delivery in ‘real time’ (as and when desired) through mobile-optimized materials [18], which might enhance the generalizability of learning across new contexts.

It has been suggested that a successful method of enhancing access and availability of psychological interventions is to implement ‘task-shifting’ or ‘task-sharing’ strategies [2]. These involve training nonspecialist individuals (such as peers or non-mental health professionals) to deliver psychological interventions [19]. We have successfully implemented this approach in the treatment of anorexia nervosa by having people with caregiving experience share their skills with other families [20,21]. The positive results from this approach support the use of peer-based guidance or mentorship as part of a self-care intervention for anorexia nervosa. This strategy is consistent with the philosophy of the *recovery approach*, which has been embraced as national mental health policy in England [22] and Scotland [23]. According to this approach, peer support is one of the five main processes of recovery, alongside hope or optimism about the future and confidence to change, development of identity, having a sense of meaning in life, and experiencing empowerment [24]. Connecting with others with similar problems, sharing skills and choosing recovery goals are key processes within this approach [25]. The use of peer support is also advocated by self-determination theory, which posits that autonomy, self-competence and relatedness to others are the bases that drive internal motivation and growth [26]. Research in eating disorders has linked perceived autonomy support from parents, staff and treatment peers to higher motivation to change [27,28] and greater self-compassion [27], whereas low self-efficacy impairs treatment outcomes [29]. Relatedness is also gravely compromised in anorexia nervosa, with loneliness [30] and poor social relationships [31] serving as causal and maintaining factors [31]. Thus, the use of peer mentors is not only linked with increased access and availability of interventions, but also offers a theoretically grounded approach for helping individuals with anorexia nervosa.

*Recovery* MANTRA integrates two novel strategies to provide peer support to individuals with anorexia nervosa. The first strategy involves offering a library of recorded personal recovery narratives (derived from interviews with formerly ill individuals) that describe successful change steps and the nonlinear process of recovery. A feasibility and acceptability study of an early prototype of the guided self-help intervention in a community sample of participants with anorexia nervosa was promising; participants exhibited weight increases and symptom improvement subsequent to the intervention [32]. Previous test trials have demonstrated that watching similar video podcasts (‘vodcasts’) to support eating or improve positive mood lead to increases in test meal consumption and reductions in anxiety and negative thoughts [33,34]. Feedback from participants, carers, and professionals has led to improvements in these materials [18].

The second strategy to provide peer support in *Recovery* MANTRA involves weekly text-based guidance from peer mentors with personal experience of eating disorders. These online guidance sessions are designed to enhance motivation and complement the participant’s use of a self-care workbook. Preliminary evidence regarding the use of peer mentors for psychological interventions is encouraging. For instance, a Cochrane systematic review examining evidence of the effectiveness of consumer providers of care concluded that these providers were as effective as statutory mental health services [35]. Moreover, the use of peer mentors as support for people with eating disorders has been found to improve these people’s quality of life and increase adherence with services [36]. However, the quality of the guidance has been found to be an important factor in shared information approaches [5] and thus rigorous, standardized training and supervision of peer mentors is an integral component of delivering an efficacious intervention. Indeed, research suggests that training of nonspecialized professionals is an important factor in enhancing feasibility of task-sharing interventions [37]. We have previously had success in training people with experience of eating disorders (mainly as caregivers) to provide a form of motivational interview-based support to other families [38] and will therefore follow the same strategy for training peer mentors in *Recovery* MANTRA.

The objectives of the aforementioned strategies for peer mentorship are to inspire, illustrate and model change for individuals with anorexia nervosa. These strategies focus *Recovery* MANTRA intervention efforts on modifiable processes, such as motivation and confidence to change, adherence to treatment, social adjustment, and mood early in treatment, and may therefore enhance treatment outcomes as compared with treatment as usual. Figure 1 outlines how the elements of the *Recovery* MANTRA intervention will target the hypothesized moderators and mediators of change within our model.

**Figure 1 Fig1:**
[figure not shown]
Participants’ and peer mentors’ confounders, moderators and mediators, and primary and secondary outcome measures for *Recovery* MANTRA. BMI, body mass index.

### *Recovery* MANTRA: study aims and research questions

The aims of the current study are threefold: (1) to assess the impact of adjunct *Recovery* MANTRA on body mass index (BMI) and eating disorder symptoms for adults in the early stages of outpatient treatment for anorexia nervosa; (2) to assess the impact of *Recovery* MANTRA on theorized mechanisms of change (and thereby evaluate mediators and moderators of BMI and eating disorder symptom outcomes), and (3) to assess the acceptability, feasibility, and treatment fidelity for the intervention and the impact of providing guidance on peer mentors’ own BMI and eating disorder symptoms. Specifically, the primary, secondary, tertiary, and exploratory research questions are outlined as follows.

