#### Exploratory

To what extent are peer mentors able to adhere to the intervention guidelines and provide guidance or support in a theoretically supported, consistent manner? Further, what is the impact of guidance delivery on eating disorder symptoms and mood among the peer mentors?How do participants and peer mentors rate the acceptability and utility of the intervention?Do ratings of treatment adherence or fidelity and acceptability predict outcomes at 6-month follow-up?

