In total, 10 to 15 peer mentors will be trained, to allow for attrition. The purpose of the guidance is not to provide an additional stand-alone intervention, but rather, to offer support to patients in using the self-help materials effectively and purposefully. Peer mentors are individuals with past experience of eating disorders who have sufficient time for training, supervision and coaching and are trained in professions allied to medicine or equivalent (psychology, counselling) or teaching. Individuals with clinically significant levels of baseline anxiety, depression or eating disorder symptoms are excluded. Comprehensive training for task-sharing interventions involves three important components: participation in an introductory workshop delivered by an expert, reading or review of workbooks or other written materials that detail the intervention, and administration of the intervention under close supervision of treatment experts [2]. Peer mentors will receive all of these training components prior to delivering the *Recovery* MANTRA intervention.

The curriculum currently used for training and supervision of carer coaches will be adapted for training peer mentors. In particular, the peer mentors will receive three days of training in motivational interviewing, during which they will also become familiarized with the *Recovery* MANTRA materials and practise using the online text-chat delivery system. For the duration of their involvement in the project, the peer mentors will also receive weekly clinical supervision and will undergo regular assessment of their eating disorder symptoms and mood. Copies of the text-chat messages between the peer mentor and the participant will be used for supervision and to assess treatment quality and fidelity.

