### Peer mentor assessments

Peer mentors will complete a demographic questionnaire upon enrolment and the EDE-QS and DASS-21 at baseline and every 3 months for the duration of their involvement in the project.

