### Outcome assessment

The primary outcome variable is patient BMI at the end of the 6-week intervention (treatment as usual versus *Recovery* MANTRA). The secondary outcome variables are patient BMI at 6-month and follow-up and eating disorder symptoms (assessed by EDE-Q scores) at 6-week and 6-month follow-up (treatment as usual versus *Recovery* MANTRA). The hypothesized mediators and moderators of primary and secondary outcomes include mood (DASS-21), perceived work or social adjustment (Work and Social Adjustment Scale), motivation and confidence to change (visual analogue scale and ACMTQ), cognitive flexibility, and perceived alliance with therapist and peer mentor. Moreover, the trajectories of change in eating disorder symptoms (weekly EDE-QS), perceived alliance with peer mentors (assessed weekly), and mood, confidence or motivation, connection to others, hope and adherence or satisfaction with treatment plan (assessed daily via ultra-brief surveys) will predict the primary and secondary outcomes. Exploratory outcomes include the impact of guidance delivery on peer mentors’ eating disorder symptoms and mood (assessed via a feedback form) and treatment adherence or fidelity and acceptability (assessed via a feedback form) on secondary outcomes.

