#### Qualitative studies A and B

Participants (*n* = 75) and peer mentors (*n* = 10 to 15) will be asked to complete a feedback form at the end of the intervention. Questions will focus on overall experience of participation, use and acceptability of materials, relationship with peer mentor or participant, any particular learning points, challenges met, and suggestions for improvement. A thematic analysis will be used to analyze data from the written feedback forms [55].

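### Aim 3 includes the effect of giving guidance on peer mentors' own BMI, but no mentor weight or BMI measurement is described, and the outcome section does not name the scored scales for mentor symptoms and mood

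*Protocol article*

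**What the plan says.** All references are to the Protocol article.

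- **Study aims and research questions.** The last clause of aim 3 covers the effect of providing guidance on mentors' "own BMI and eating disorder symptoms".
- **Exploratory research questions.** The specific question is "what is the impact of guidance delivery on eating disorder symptoms and mood among the peer mentors". BMI is not named.
- **Guided self-help, paragraphs on mentor training and supervision.** Mentors "will undergo regular assessment of their eating disorder symptoms and mood". BMI is not named.
- **Peer mentor assessments.** "Peer mentors will complete a demographic questionnaire upon enrolment", and then the "EDE-QS and DASS-21 at baseline and every 3 months for the duration of their involvement in the project".
- **Outcome assessment.** The exploratory mentor outcome is the impact on "eating disorder symptoms and mood (assessed via a feedback form"). No scale is named.
- **Subsidiary analysis of peer mentors.** Changes in mentor symptoms, with mood and eating as examples, are to be assessed. BMI is not named.
- **Qualitative studies A and B.** The feedback form is filled in at the end of the intervention and analysed thematically. "Questions will focus on overall experience of participation, use and acceptability of materials", along with the mentor-participant relationship, learning points, challenges and suggestions.

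**The concern.** An aim can be answered only if its outcome is measured. Here BMI is stated as part of an aim, but it does not appear in the mentor schedule, the mentor outcome or the mentor analysis. Anyone running the trial from this text would reach the end without mentor BMI to report.

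Symptoms and mood raise a different problem, because two sections name different sources for the same outcome. One gives repeated scored scales; the other gives only a form described as a written, end-of-intervention account. An analyst who followed Outcome assessment alone would have no baseline from which to judge change.

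What is at stake is whether the trial can report what it says it will about mentors, who have past experience of eating disorders. No patient outcome is involved.

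**Working it through.** No sample size, power or other figure is at issue, so the check sets the sections side by side.

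**1. Mentor BMI**

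| Section | Mentor BMI or weight | Mentor symptoms and/or mood |
|---|---|---|
| Aim 3 | named | symptoms named |
| Exploratory question | not named | both named |
| Mentor supervision and monitoring (Guided self-help) | not named | both named |
| Peer mentor assessments | not named | EDE-QS, DASS-21 |
| Outcome assessment | not named | both named |
| Subsidiary analysis of peer mentors | not named | both named as examples |

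Mentor BMI appears in one of these six places, the aim, and in none of the five that would put it into effect.

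No listed instrument fills the gap:

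- Patient assessments describes the EDE-QS as a 12-item measure of eating disorder symptoms and the DASS-21 as a 21-item measure of depression, anxiety and stress. Neither is described as yielding BMI.
- The same section describes clinician weighing and self-reported BMI at 6 months for patients only.
- The demographic questionnaire's items are not listed. Even if it asked for height and weight, it is completed once, at enrolment, and one reading cannot show an effect of giving guidance.

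**2. Source for mentor symptoms and mood**

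| Feature | Peer mentor assessments | Feedback form (Outcome assessment; Qualitative studies A and B) |
|---|---|---|
| Content | scored symptom and mood scales | experience, acceptability, relationship, challenges, suggestions |
| Timing | baseline and every 3 months | end of the intervention |
| Analysis | changes in symptoms (Subsidiary analysis of peer mentors) | thematic |
| Can show change from baseline | yes | not as described |

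The data needed for symptoms and mood are therefore scheduled. The defect is that Outcome assessment does not point to them.

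**The case against.** The strongest reply is that BMI in aim 3 is a stray word in a summary sentence. The article says that its specific questions follow the aims, and the specific mentor question names symptoms and mood only. The monitoring, outcome and analysis sections do the same. This may well be the explanation. It supports deleting the word as one of the two remedies, but it does not remove the mismatch while the aim stands.

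A second reply is that mentor feedback is a deliberate source. The abstract says feedback is gathered to understand the effect on mentors' own well-being, and Limitations and challenges says it will be used. This stands. A reader might infer that the feedback form is simply the wrong instrument, or that it does not touch symptoms at all. The documents do not support that: the form's items are not shown, and the description of its focus is a summary. What can be said is that, as described, it does not provide repeated scored measurement.

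A third tempting inference is that mentors' safety is left unwatched, or that one of the trial's three aims fails. Neither holds. People with clinically significant baseline anxiety, depression or eating disorder symptoms are excluded as mentors. Those enrolled have weekly clinical supervision and regular symptom and mood assessment. The effect on mentors is one clause of aim 3, after acceptability, feasibility and fidelity, and BMI is one part of that clause.

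Finally, the article condenses a fuller protocol, and Figure 1, whose caption covers mentor measures, is not available. This is why the point is that no mentor BMI measurement is described, not that none was ever taken. Condensation can excuse missing detail, but it does not reconcile an aim, a schedule and an outcome source that disagree in the same text. Listing BMI in Figure 1 would not put it on the schedule.

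**Conclusion.** The point holds in a limited form. The part of aim 3 that concerns mentors' BMI cannot be answered from the assessments described. Outcome assessment names only a feedback form for mentor symptoms and mood, although Peer mentor assessments already schedules scored scales that can show change. The first is an unmeasured component of an aim; the second is a mismatch of sources, not missing data.

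The size is small. The question is exploratory, it concerns 10 to 15 mentors, and it affects neither the primary BMI comparison nor any secondary comparison in patients. No comparison group of mentors is described, so even complete data would describe change over time and would not isolate the effect of giving guidance.

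The conclusion assumes that the mentor schedule as printed is complete.

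**What to change.** 1. **Reconcile aim 3 with the mentor schedule.** Preferably, add self-reported height and weight to the existing baseline and 3-monthly mentor questionnaires, and add BMI to the exploratory mentor question, Outcome assessment and the subsidiary mentor analysis. Self-reported BMI is already accepted for patients at 6 months. The cost is two extra items for each of 10 to 15 mentors. Otherwise, delete mentor BMI from aim 3, which costs a wording change and gives up that part of the question. The choice should be made promptly, because a baseline reading cannot be taken once a mentor has begun giving guidance.
2. **Correct the source in Outcome assessment.** Name the EDE-QS and DASS-21, as scheduled under Peer mentor assessments, as the measures of change in mentor symptoms and mood. Keep the feedback form as a supplementary qualitative source. This is a wording change only and needs no new data.

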#### Primary

Is *Recovery MANTRA* associated with higher BMI at the end of the 6-week intervention relative to treatment as usual alone?

#### Secondary

Is *Recovery MANTRA* associated with higher BMI at 6-month follow-up and with lower eating disorder symptoms at 6-weeks, and 6-month follow-up compared with treatment as usual alone?

#### Tertiary

Do the domains identified by the underlying cognitive-interpersonal theoretical model (including motivation, hope, and confidence to change, anxiety, stress, and depression, perceived therapeutic alliance, work and social adjustment, social support, and increased cognitive flexibility) moderate or mediate changes in primary and secondary outcomes? Does the trajectory of daily process measures and weekly eating disorder symptoms measures predict outcomes (BMI and eating disorder symptoms) at 6-month follow-up?

#### Exploratory

To what extent are peer mentors able to adhere to the intervention guidelines and provide guidance or support in a theoretically supported, consistent manner? Further, what is the impact of guidance delivery on eating disorder symptoms and mood among the peer mentors?How do participants and peer mentors rate the acceptability and utility of the intervention?Do ratings of treatment adherence or fidelity and acceptability predict outcomes at 6-month follow-up?

## Methods

### Trial design

This is a multicentre, two-arm randomized controlled study (SHARED) exploring the efficacy of adding a guided self-help intervention (*Recovery* MANTRA) to treatment as usual for anorexia nervosa. The study received ethical approval from a National Research Ethics Service Committee (London Brent, approval number 14/LO/1347) and approvals from the research and development departments at South London and Maudsley NHS Foundation Trust, Barnet Enfield & Haringey NHS Mental Health Trust, Coventry and Warwickshire Partnership NHS Trust, Surrey and Borders Partnership NHS Foundation Trust, Worcestershire Health and Care NHS Trust, Cambridgeshire and Peterborough NHS Foundation Trust, Cumbria Partnership NHS Foundation Trust, Dorset HealthCare University NHS Foundation Trust, Leicestershire Partnership NHS Trust, Lincolnshire Partnership NHS Foundation Trust, South Essex Partnership University NHS Foundation Trust, Nottinghamshire Healthcare NHS Trust, Sussex Partnership NHS Foundation Trust and Kent and Medway NHS Trust. Recruitment will not begin at any individual centre until all approvals have been obtained.

After providing informed consent, participants are randomly assigned to either (1) *Recovery* MANTRA in addition to treatment as usual (*Recovery* MANTRA condition) or (2) treatment as usual alone (control condition). Participants are recruited from over 25 different specialist adult outpatient eating disorder services in the UK. Data are collected at baseline, during the intervention, after 6 weeks (that is, at the end of the intervention for those in the *Recovery* MANTRA condition), and at 6-month follow-up (Table 1). At the end of the study, individuals who had been randomized to the treatment as usual only control condition will be offered the *Recovery* MANTRA intervention materials (that is, vodcasts and workbook).

